### Intervention scheme / trial flow

Inpatients from all trial sites that meet the inclusion criteria and give informed consent are consecutively included into the trial within one week after admission. After inclusion, inpatients will be interviewed by the blinded research psychologist. Initial self-report measurements and objective data in relation to depression and associated co-morbidity as well as medication are assessed by a trained diagnostician. In addition, treatment expectancy and responsibility to seasonal effects will be assessed. After the pre-treatment assessment (T1), patients are randomized to either a placebo control condition (PCC) or BLT. Both groups also receive TAU. Trial interventions will be delivered each morning (except weekends) over a period of four weeks about 7.5 h after the DLMO assessed with the MEQ.

During the intervention trial, an interim assessment with the BDI-II after two weeks will take place in order to control patient-perceived changes in depression more closely. There is no full assessment in order to reduce stress for the patients. Four weeks after completion of the treatment, individuals will again be interviewed by the blinded research psychologist and score the self-rating questionnaires as well as perform the neuropsychological assessment and deliver saliva melatonin and cortisol (post-treatment assessment; T2). Three and six months after T2, follow-up assessments will be performed via telephone and questionnaires to control for stability (T3 and T4). There is no full reassessment for neurobiological and neuropsychological data in order to facilitate the response to fulfil the follow-up assessment and to meet patients’ needs best. Moreover, AEs will be assessed in both treatment groups on a weekly basis. For an overview of the trial flow, see Fig. 1. For details on procedures per time point, see Figs. 2 and 3.

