### Data analysis

#### Proposed sample size/power calculations

In our pilot study [20], a similar trial design was used, investigating the effects of BLT versus placebo light therapy after a treatment period of 14 days and a follow-up period of three weeks. Remission rates at the end of follow-up (week 5) were 46.7% for BLT and 25.9% for dim light. These remission rates were transformed (2*arcsin; √remission rate). The difference between the transformed remission rates resulted in Cohens h of 0.437 and was used for the calculation of the study sample. A significant difference between the two groups is defined as 3 points on the BDI-II by the NICE guidelines. A standard deviation of 10 points in the BDI-II is assumed. Thus, the proposed study aims to show a group difference of 4.37 points on the BDI-II. Calculations based on this difference yield a sample size of 224 patients (112 for each group) when using an independent t-test at a significance level of 5% and a power of 90%. Sample size was calculated using PROC POWER in SAS® Version 9.4. Drop-outs will be analyzed using multiple imputation methods.

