#### Statistical analyses

The primary analysis population is the intention-to-treat (ITT) population comprising all randomized patients. Group difference in change of BDI-II rating under trial treatment will be analyzed by an analysis of covariance (ANCOVA) comprising the covariates baseline BDI-II rating, treatment group, prior pharmacological antidepressant therapy (yes/no), and sex. Missing values will be replaced by multiple imputation. The two-sided level of significance will be α = 5%. Supportive analyses are planned for the Per Protocol Population and the Completer Population. The Per Protocol Population comprises all patients from the ITT population without major protocol violations: lack of compliance with regard to therapy sessions; not meeting all inclusion criteria; meeting at least one exclusion criterion; intake of unallowed concomitant medication during the study; end of treatment visit out of schedule. In an additional sensitivity analysis, missing values will be analyzed based on the last available BDI-II rating (Last Observation Carried Forward [LOCF]). In case the LOCF approach turns out to be not conservative, an additional Baseline Observation Carried Forward (BOCF) analysis will be performed.

Further subgroup analyses are planned to detect possible differences between predictive factors (e.g. trial site, concomitant psychotropic medication for co-morbid disorders, baseline CAR and DLMO, type of depression [seasonal/non-seasonal], season, expectancy questionnaire). No interim analyses are planned. Secondary endpoints will be analyzed descriptively applying appropriate methods depending on the scale of the respective parameter. Interpretation of statistical tests must be exploratory except for the primary outcome.

AEs will be coded according to MedDRA terminology. Detailed information collected for each AE will include: a description of the event; duration; whether the AE was serious; intensity; relationship to trial treatment; action taken; and clinical outcome. Summary tables will present the number of participants observed with AEs by MedDRA System Organ Class and Preferred Term and corresponding percentages. Additional subcategories will be based on event intensity and relationship to trial treatment. A subject listing of all AEs will be prepared.

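### BOCF is added only if LOCF proves not conservative: the trigger has no stated criterion, and with more placebo drop-out BOCF favours BLT more than LOCF does

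*Protocol article*

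**What the plan says.** All points are from the protocol article.

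- **Primary analysis** (Statistical analyses): ANCOVA of BDI-II change in all randomized patients, at a two-sided 5% level. "Missing values will be replaced by multiple imputation".
- **Missing-data sensitivity analysis** (same section): LOCF, using each patient's most recent BDI-II score. No other sensitivity analysis for missing values is named. The Per Protocol and Completer analyses change the population instead.
- **Conditional step** (same section): "In case the LOCF approach turns out to be not conservative, an additional Baseline Observation Carried Forward (BOCF) analysis will be performed". No criterion, time point or blinding status accompanies it.
- **Scores available to carry forward** (Intervention scheme / trial flow): baseline, and one intermediate score, since "an interim assessment with the BDI-II after two weeks will take place". The same section says that both arms receive treatment as usual (TAU).
- **A route to missing data** (Interventions): patients who miss too many sessions leave the study, under the same rule in both arms.

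**The concern.** A sensitivity analysis should be fixed before the results are known and should test the assumption that the primary analysis rests on. This rule is weak on both counts.

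First, whether the second analysis is run hangs on an undefined judgement about the first. A reader of the final report could not tell whether BOCF was present or absent because of a prior rule or because of what the data showed.

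Second, the order presumes that BOCF is the stricter method. Patients in both arms receive inpatient treatment and may well improve. Carrying an early score forward then penalises whichever arm loses more patients. If that is the placebo arm, LOCF leans toward BLT and BOCF leans further the same way. The fallback would then make worse the fault that triggered it.

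At stake is the supporting evidence on robustness, which could look reassuring, or alarming, for reasons unrelated to the treatment.

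**Working it through.** **1. The plan's own figure.** The design uses a difference of 4.37 points ("Thus, the proposed study aims to show a group difference of 4.37 points on the BDI-II") and an SD of 10 ("A standard deviation of 10 points in the BDI-II is assumed"). The exact two-sided 5% t-test has power 0.89997 with 111 per arm and 0.9025 with 112. So 112 per arm, 224 in total, reproduces. Nothing below alters it.

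**2. Assumptions.** The article gives no drop-out rates, mean improvement or correlations. These are assumed:

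- I4 = mean improvement by T2, 10 points in both arms; I2 = improvement by week 2, 5 points
- d_B, d_P = drop-out proportions on BLT and placebo
- e = share of drop-outs who leave before the week-2 score
- drop-out is random within each arm

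**3. Shift toward BLT when there is no true effect.**

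BOCF gives every drop-out zero improvement:

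shift = (d_P − d_B) × I4 = (0.20 − 0.10) × 10 = **1.0 point**

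LOCF loses I4 for those who leave before week 2, and I4 − I2 for the rest:

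shift = (d_P − d_B) × [e × I4 + (1 − e) × (I4 − I2)]

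- e = 0 (every drop-out has a week-2 score): 0.10 × 5 = **0.5**
- e = 0.5: 0.10 × (0.5 × 10 + 0.5 × 5) = **0.75**

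Against the 3-point relevant difference, 1.0 point is 33% and 0.5 to 0.75 points is 17% to 25%. For improvements of 6 to 12 points, the BOCF shift runs from 0.10 × 6 = 0.6 to 0.10 × 12 = 1.2 points.

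**4. Simulation of the baseline-adjusted ANCOVA.** Settings: 112 per arm, SD 10, correlation 0.5 between baseline and later scores and 0.7 between week 2 and T2, e = 0.5, 2,000 replicates per scenario, no true effect, I4 = 10. In brackets is the chance of a significant result favouring BLT (nominal 2.5%).

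| Drop-out BLT / placebo | LOCF shift | BOCF shift |
|---|---|---|
| 15% / 15% | −0.03 (2.1%) | −0.02 (2.4%) |
| 10% / 20% | +0.73 (10.2%) | +0.97 (13.8%) |
| 10% / 30% | +1.51 (24.0%) | +2.02 (38.8%) |
| 20% / 10% | −0.80 (0.2%) | −1.06 (0.1%) |

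In the 10% / 20% scenario, an analysis of completers only gave −0.03 points (3.0%). The shift therefore comes from carrying scores forward, not from selective loss of patients.

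**5. With a true effect of 4.37 points.** The BOCF estimate is (1 − d_B) × (I4 + 4.37) − (1 − d_P) × I4.

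- 15% / 15%: 0.85 × 14.37 − 0.85 × 10 = 3.71 (simulated: BOCF 3.70, LOCF 3.86)
- 20% / 10%: 0.80 × 14.37 − 0.90 × 10 = 2.50 (simulated: BOCF 2.49, LOCF 2.96)
- 10% / 30%: 0.90 × 14.37 − 0.70 × 10 = 5.93 (simulated: BOCF 5.93, LOCF 5.55)

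In the first two cases both methods understate the effect. In the third both overstate it, BOCF by more.

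**The case against.** **The reach is limited.** The primary analysis is multiple imputation, LOCF is run in every case, and BOCF is added without replacing anything. No rule lets either override the primary result. This stands: a reader might infer that the primary test or its type I error is compromised, and the document does not support that.

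**The trigger need not depend on the unblinded effect.** A reader might infer that conservatism can be judged only once the treatment effect is known. The article does not say so. The pooled BDI-II course and the pooled amount and timing of drop-out can be reviewed blinded, and drop-out by arm needs allocation but not the effect. A statistical analysis plan, not shown here, might define the criterion. This also stands. What remains is that the published rule, as worded, allows a results-dependent choice.

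**Both methods can be conservative.** A reader might infer that they always favour BLT. They do not: equal drop-out, or more on BLT, makes them neutral or unfavourable to BLT. The article gives no reason to expect more placebo drop-out, since the glasses are identical, patients are blinded and the missed-session rule is common to both arms. So the direction is unknown, and for that reason neither method can be relied on as conservative.

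**Two further charges should not be pressed.** The first is that carry-forward materially understates the standard error. In a check with no true effect and 15% random drop-out per arm (8,000 replicates), model and empirical standard errors were 1.177 and 1.190 for LOCF and 1.193 and 1.210 for BOCF. The gap is about 1%, as with complete data (1.157 and 1.169). The second is that neither method departs from missing at random. BOCF is itself one such departure; what is lacking is a graded one.

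**Conclusion.** The point holds as a fault in a stated rule. The condition for adding BOCF is undefined, and the order LOCF then BOCF does not guarantee greater caution. With more placebo drop-out and improvement in both arms, BOCF leans further toward BLT than LOCF: about 1.0 against 0.5 to 0.75 points in the 10% / 20% example with a 10-point improvement. The signs reverse when BLT loses more patients, and under no effect the shift vanishes when drop-out and its timing are equal. These sizes rest wholly on assumed drop-out and improvement; the mechanism does not depend on the particular values.

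Neither analysis tells the reader how large a departure from missing at random, the usual assumption behind multiple imputation, would overturn the conclusion. This is a worthwhile, low-cost improvement to the supporting analyses. It is not a threat to the primary analysis, the significance level or N = 224.

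**What to change.** In Statistical analyses, delete the sentence that makes BOCF conditional. Name one unconditional missing-data sensitivity analysis: delta-adjusted multiple imputation with the same ANCOVA. Imputed T2 BDI-II scores in the BLT arm are worsened in fixed steps, for example from 0 to 10 points, and the report gives the estimate at each step and the delta at which significance is lost. The range should extend until that point is reached: with 10% missing on BLT, a delta of 10 moves the estimate by only 0.10 × 10 = 1.0 point.

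If LOCF or BOCF is kept for comparison with older trials, run and report it whatever the results, next to drop-out numbers and timing by arm, and do not call it conservative in advance.

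This is one option among acceptable ones; reference-based imputation set out in advance would also serve. The change should be made before unblinding. It costs a wording change and a little analysis code, with no new data, visits or patients.

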## Discussion

In this study protocol, we presented the background, design, measurements, and statistical procedures of our randomized, controlled, double-blind multicenter parallel group trial of BLT in a naturalistic inpatient setting. We discussed the medical problems regarding treatment and remission rates in adolescents meeting the criteria of depression and constituted the need to close the gap of evidence of BLT in youth therapy by prolonged (four weeks) intervention time and minimized bias problems due to our randomized, double-blind design.

There are several limitations the study will have to deal with, e.g. the exclusion of the weekends during intervention periods or lack of evidence for actual wearing time of the glasses because of the naturalistic setting. An additional disadvantage is the already regulated sleep-wake rhythm due to the inpatient setting, making a larger difference between activity- and sleep-times among the patients of the two treatment groups difficult to emerge. Moreover, the strict schedules at the infirmaries limit the power of the results compared to a more realistic, ambulant setting.

As remission rates of state-of-the-art treatments for depressed adolescents such as cognitive behavioral therapy and antidepressants remain unsatisfactory, and due to its easy application, low side effects, and optimized compliance, BLT seems to be a promising add-on therapy to psychological and pharmacological approaches to increase standard treatment effects. Since previous studies investigating the effect of BLT in depressed adolescents suffer from small sample sizes, the results of this projected trial will be of great importance.

### Trial status

Recruitment is planned to begin in February 2018.

## Abbreviations

ANCOVA: Analysis of covariance
BDI-II: Beck Depression Inventory II
BLT: Bright light therapy
BOCF: Baseline Observation Carried Forward
CAR: Cortisol awakening response
CDRS - R: Children’s Depression Rating Scale – Revised
CGI-I: Clinical Global Impression-Improvement
CGI-S: Clinical Global Impression-Severity
CHIP – AE: Child Health and Illness Profile-Adolescent Edition
DALYs: Disability Adjusted Life Years
DGKJP: German Association for Child and Adolescent Psychiatry
DLMO: Dim light melatonin onset
HRQoL: Health-related quality of life
ICH-GCP: International Council for Harmonization of Technical Requirements for Pharmaceuticals for Human Use (ICH) - Good Clinical Practice
ITT: Intention-to-treat
IZKS: Interdisziplinäres Zentrums Klinische Studien
KIGGS: Studie zur Gesundheit von Kindern und Jugendlichen in Deutschland
LOCF: Last Observation Carried Forward
MedDRA: Medical Dictionary for Regulatory Activities
MEQ: Morningness–Eveningness Questionnaire
NICE: National Institute for Health and Care Excellence
PCC: Placebo control condition
SAD: Seasonal affective disorder
SAE: Serious adverse events
SDQ: Strengths and Difficulties Questionnaire
SF-B/R: Schlaffragebogen B – Revidierte Fassung
SPAQ: Seasonal Pattern Assessment Questionnaire
T1: Pre-treatment assessment
T2: Post-treatment assessment after four weeks
T3: Post-treatment assessment after three months
T4: Post-treatment assessment after six months
TADS: Treatment of adolescents with depression study
TAP: Testbatterie zur Aufmerksamkeitsprüfung
TAU: Treatment as usual
TORDIA: Treatment of resistant depression in adolescents
UKE: Universitätsklinikum Hamburg-Eppendorf
